## Introduction

### Background and rationale

Functional deficits (i.e. social skills, community functioning) are a core feature of schizophrenia. They represent key diagnostic criteria for the disorder that precede illness onset and are a strong predictor of outcome. These deficits do not respond to current psychopharmacology [1–3], thus underscoring the need to develop alternative interventions such as psychosocial treatments to address functional impairments.

Over the last 15 years, there has been renewed awareness of the impact of cognitive impairment in schizophrenia and the effect these deficits have on recovery and treatment outcomes [4, 5]. Compensation and adaptation therapies have been defined as “behavioural training-based intervention that aims to improve cognitive processes (attention, memory, executive functioning, social cognition or meta cognition with the goal of durability and generalisation)” [6]. A meta-analysis published in 2011 demonstrated that compensation and adaptation therapies had an overall effect size of 0.45 on global cognition with larger effect when combined with adjunctive rehabilitation (ES = 0.59) [6].

The research to date has not been able to refine who responds to cognitive compensation and adaptation therapies. There is interest in objective tests such as electroencephalography (EEG). EEG findings of attenuation in mismatch negativity (MMN) in auditory oddball tasks are one of the most robust and replicable neurophysiological markers of schizophrenia [7]. The MMN response occurs when a rare, unexpected sound is played in a repetitive sequence of sounds and is thought to reflect a brain response to an error in what is predicted. This sensory prediction error response has also been shown to relate to functional ability in people at risk for schizophrenia [8]. There are pilot studies indicating it may be able to predict and be an objective indicator of people who would benefit from psychosocial interventions [9–11]. Being able to have more precise information on who would respond to interventions, especially psychosocial interventions that require a weekly commitment over months, would benefit participants and not expose people to the potentially demoralising effect of attending a therapy that they were not able to benefit from [12].

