### Outcomes

A battery of validated clinical measures will be conducted at baseline, at post-treatment, and at 3-month follow-up. Raters who are blind to the randomisation of condition (registered psychologists) will complete the measures. The assessors instruct the participant not to reveal their group allocation.

The following measures will be used:
Brief Assessment of Cognition in Schizophrenia (BACS) [17] is an instrument that assesses the aspects of cognition found to be most impaired and most strongly correlated with outcome in patients with schizophrenia. This is the primary outcome measure.Test of Premorbid Functioning (TOPF) [18] is a test of premorbid intelligence as estimated from reading ability.Subjective Scale to Investigate Cognition in Schizophrenia (SSTICS) [19]. This measures the perception of cognitive abilities when completing everyday tasks.Social Functioning Scale (SFS) [20] assesses areas of functioning that are crucial to the community maintenance of individuals with schizophrenia.Brief Psychiatric Rating Scale (BPRS) [21] is a widely used scale for measuring symptom severity of patients with schizophrenia.Electroencephalography (EEG). Participants will listen to a duration auditory oddball paradigm while their brain responses are measured with EEG. An auditory oddball paradigm consists of presentations of sequences of predictable sound stimuli (standard sounds) that are infrequently interrupted by unpredictable sound stimuli (deviant sounds). Sounds will be delivered via headphones and will vary in duration. All tones will be presented in a sound range that is comfortable for the participants. In the “volatility” auditory oddball task, the participants will be asked to pay attention to the sounds in order to judge the proportion of different sound types and rate their confidence on this judgement. This will allow us to assess the ability of participants to learn the statistical relationships of sound types, as well as the confidence on their own judgement. Prior to the experiment, the participants will be familiarised with the different sound types and trained with two short practice tasks. Participants will make responses using a computer keyboard and a mouse. The duration of the practice task will be 2 min, and the duration of the volatility auditory oddball task will be approximately 18 min, with a total duration of testing of approximately 20 min per participant, including breaks.

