### Cognitive intervention-related changes in brain and behaviour: single-channel and behavioural analyses

To investigate if MMN improves after the compensation and adaptation therapy programmes, we will conduct a repeated measures 2 × 2 × 3 ANOVA design on mean ERP values, with MMN volatility (stable and volatile), treatment (CCT or CIRCuiTS), and visit (baseline, 12 and 24 weeks) as factors. Responders will be participants who make a clinically significant positive change based on the measures of cognition collected using Jacobson and Truax’s Reliable Change Index [22]. Mean ERP values will be obtained by averaging across the preselected time window of interest for MMN latency: 100–250 ms, over a frontocentral channel (Fz) [23]. In addition, we will investigate the behaviour, “regularity learning”, which is found to underlie the MMN response. We will conduct a separate repeated measures 2 × 2 × 3 ANOVA design with the following factors: regularity learning (stable and volatile), treatment (CCT or CIRCuiTS), and visit (baseline, 12 and 24 weeks). This behavioural analysis will be conducted to examine if the compensation and adaptation therapy programmes improve regularity learning ability. Significant interactions will be further analysed using paired *t* tests.

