### Predicting cognitive intervention response with machine learning: spatiotemporal maps and feature definition

To identify if EEG measures can be used to predict response to the compensation and adaptation therapies, we will use machine learning techniques to classify individual patients that benefit from the compensation and adaptation therapies (responders) from patients who do not improve after the compensation and adaptation therapies (non-responders). Machine learning will be implemented using the Pattern Recognition for Neuroimaging Toolbox (PRoNTo) [23] with features from the whole-brain spatiotemporal analysis. First, we will create three-dimensional spatiotemporal images from averaged ERP data. A three-dimensional matrix (32 × 32 × 81) corresponding to the scalp electrode space and time points will be constructed, per participant for the different conditions. The images will be smoothed at full width half maximum of 12 mm × 12 mm × 20 ms. Before conducting the machine learning, we will perform the standard spatiotemporal mass-univariate general linear model analysis. A full factorial analysis will be performed to examine the spatiotemporal changes after the therapy programmes, with the following factors: volatility (stable and volatile), treatment (CCT or CIRCuiTS), and visit (baseline, 12 and 24 weeks). All statistical maps will be thresholded at *p* < 0.05 family-wise error (FWE) corrected for multiple comparisons.

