Next, we will conduct the machine learning analysis, and the three-dimensional spatiotemporal images will be fed as features into the classifier. To classify the compensation and adaptation therapy responders and non-responders, class labels will be assigned to each participant. In PRoNTo, we will apply the support vector machine (SVM) and Gaussian process algorithms [24], which has shown to be effective in classifying schizophrenia patients using neuroimaging features [12]. The SVM training phase involves assigning weights to features and finding the hyperplane that maximises the margin between the groups of participants; the sign of the total feature weights multiplied by the test sample will determine the classification of participants. A *k*-fold cross-validation scheme will be conducted, dividing the group of participants into *k* subgroups, and iteratively assigning subgroups for training or testing until all subgroups have been through the testing. Mean-centering will be performed on all models and normalisation will be applied. In order to attain statistical measures, permutation tests will be performed (1000 repetitions) for each model and cross-validation scheme. To correct for multiple comparisons, we will apply false discovery rate correction of *q* = 0.05. Model sensitivity and specificity will be determined using the receiver operating characteristic curve, which will show the true positive rate (sensitivity) as a function of false positive rate (1 − specificity). The area under the curve will determine how well we are able to differentiate between compensation and adaptation therapy responders and non-responders using the best classifier from the EEG data.

Finally, we will conduct regression modelling to examine model performance by comparing true compensation and adaptation therapies’ response with that response predicted by the model. Spatiotemporal images for each subject will be mapped to their BACS scores, and machine learning regression algorithm—Kernel Ridge Regression [25, 26]—will be trained to predict these scores. To determine the accuracy of predicted response to compensation and adaptation therapies, we will calculate mean-squared error, Pearson’s correlation, and coefficient of determination statistics. Again *k*-fold cross-validation will be applied, permutations will be conducted to attain statistical measures, and multiple comparisons will be Bonferroni corrected.

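### The responder label partly encodes baseline cognition and is read as benefit versus no improvement, so above-chance EEG classification would not by itself show prediction of treatment response

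*Protocol article*

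**What the plan says.** The responder rule stands in the section on single-channel and behavioural analyses of the protocol article: "Responders will be participants who make a clinically significant positive change based on the measures of cognition collected", by the Reliable Change Index. No practice-adjusted variant is named.

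The section on predicting response with machine learning uses the rule to "classify individual patients that benefit from the compensation and adaptation therapies (responders) from patients who do not improve". There, "class labels will be assigned to each participant", and a support vector machine and a Gaussian process classifier are trained on EEG images. Significance comes from 1000 label permutations with false discovery rate correction, and performance from the ROC curve and its AUC. No comparison with a non-EEG predictor is planned. A separate kernel ridge regression maps the EEG images to BACS scores.

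Under Outcomes the article says: "A battery of validated clinical measures will be conducted at baseline, at post-treatment, and at 3-month follow-up". The BACS (performance, primary outcome) and the SSTICS (self-report) both concern cognition. Both randomised arms receive an active programme.

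**The concern.** The aim is to learn whether baseline MMN tells us who will benefit. Three features of the label bear on that.

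1. **Baseline content.** Change is follow-up minus baseline. A participant whose baseline score happened to fall below their usual level tends to show a larger rise. Responders will therefore have lower baseline scores on average even if therapy does nothing. A permutation test breaks every link between features and label at once, so it cannot tell an EEG signal for treatment response from one that tracks the baseline score.
2. **Meaning of the negative class.** The index asks whether change exceeds measurement error. Not exceeding it is compatible with real improvement.
3. **Attribution.** The BACS is given three times and there is no untreated arm, so a reliable rise may be therapy, retest gain or both.

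At stake is the reading of a positive EEG result as individual prediction of benefit from therapy.

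**Working it through.** **What the article gives.** The only related figure is the number of completers: 100 × (1 − 0.20) = 80, and 100 × (1 − 0.15) = 85, so the stated value of about 80 matches the 20% end. No cut-off, reliability or responder rate is given.

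**Assumptions.** BACS is scaled to SD 1 with equal variance at each visit. Retest reliability r is 0.70 to 0.95. The index takes its standard form: raw change divided by the standard error of the difference, cut at 1.96. Mean retest gain is 0 to 0.3 SD. Baseline = T + e0 and follow-up = T + gain + retest gain + e1, with var(T) = r and var(e0) = var(e1) = 1 − r, all independent and normal.

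**Step 1: threshold.** Bar = 1.96 × √(2(1 − r)). This gives 1.52, 1.24, 0.88 and 0.62 SD at r = 0.70, 0.80, 0.90 and 0.95.

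**Step 2: change and baseline.** With equal gains for everyone, cov(baseline, change) = −(1 − r) and SD(change) = √(2(1 − r)). The correlation is therefore −√((1 − r)/2): −0.39, −0.32, −0.22 and −0.16 at the same four values of r.

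**Step 3: how well baseline BACS alone separates the classes.** Simulated AUC, 2 million cases per cell, with a lower baseline score predicting response:

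| Assumed effects | r = 0.70 | 0.80 | 0.90 | 0.95 |
|---|---|---|---|---|
| No therapy effect, no retest gain | 0.75 | 0.71 | 0.65 | 0.61 |
| No therapy effect, retest gain 0.3 | 0.73 | 0.68 | 0.62 | 0.58 |
| True gain N(0.45, SD 0.45), no retest gain | 0.68 | 0.63 | 0.58 | 0.54 |
| True gain N(0.45, SD 0.45), retest gain 0.3 | 0.67 | 0.62 | 0.57 | 0.54 |

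The range is 0.54 to 0.75, where 0.50 would mean no information.

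**Step 4: who is in the negative class.** With true gain N(0.45, SD 0.45), the share of the whole sample with a true gain above zero is Φ(0.45/0.45) = Φ(1) = 84%. The share among those labelled non-responders is:

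| Retest gain | r = 0.70 | 0.80 | 0.90 | 0.95 |
|---|---|---|---|---|
| 0 | 82% | 81% | 79% | 75% |
| 0.3 SD | 81% | 79% | 74% | 64% |

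**Step 5: retest gain.** P(responder) = 1 − Φ((bar − mean change)/√(2(1 − r))). With no therapy effect and no retest gain this is 2.5% at every r. With a 0.3 SD retest gain it is 5.8%, 6.9% and 9.9% at r = 0.70, 0.80 and 0.90. Subtracting a known mean retest gain restores 2.5%, but it also lowers the total: at r = 0.80, true gain N(0.45, SD 0.45) and retest gain 0.2 SD, responders fall from 22.4% to 15.5%.

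**The case against.** Much of the case on the other side stands.

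- **Every size is assumed.** The article gives no reliability, retest gain or distribution of true gains. The highest AUCs belong to the case of no therapy effect. With real, varying gains they fall to 0.54–0.68.
- **The route from baseline score to EEG is not automatic.** In the model above, change is independent of stable cognition T; only the occasion-specific part e0 drives the link. EEG that tracks stable ability alone would gain nothing. It would gain if it shared day-to-day state with the baseline BACS, or if true gain itself depended on baseline level. Baseline BACS is thus a competing explanation to be excluded, not a demonstrated artefact.
- **The label is not worthless.** In a population half with no gain and half with a 0.9 SD gain (mean 0.45), about 86–95% of responders are true gainers at r = 0.70–0.90. Sensitivity is the weak side: 21–52% without retest gain. A reader might infer that the labels fail to identify who benefits, but these figures do not support that.
- **The bar against the effect.** A reader might also infer that the index demands two to three times the expected effect. The article states no expected change for this trial. The statement that "compensation and adaptation therapies had an overall effect size of 0.45 on global cognition" is a background meta-analytic result for the therapy class, and 0.59 stands beside it for use with adjunctive rehabilitation. Over r = 0.70–0.95 the bar is 0.62/0.59 = 1.05 to 1.52/0.45 = 3.4 times these values. Retest gain also raises the responder count while a high bar lowers it, so the two do not add up.
- **Instrument and visit.** The rule speaks of measures in the plural and names no visit, but it does not say that BACS and SSTICS, or the two later visits, are pooled, or that success on any one counts. That detail may stand in the full protocol or the analysis plan.

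None of this removes two things the article does state: the classes are described as benefit and no improvement, and the classifier is tested only against chance.

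**Conclusion.** The concern holds in a limited form. Followed as written, the plan could report above-chance EEG classification as prediction of treatment benefit when part of it reflects baseline cognition. The room for this is a baseline-only AUC of about 0.54 to 0.75 under reliability 0.70–0.95. It is small if the BACS is very reliable and true gains vary widely, and substantial if not.

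Describing the negative class as patients who do not improve is not supported by the index. Under true gains N(0.45, SD 0.45), 64–82% of that class improved, although this share follows largely from assuming that 84% of all participants do. Nor can the design say how much of a reliable rise is therapy.

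The point concerns the MMN prediction aim only. The regression on BACS scores does not need the responder label, and the primary BACS comparison is untouched. It is a cheap improvement that changes what the trial can conclude on this aim.

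**What to change.** 1. Define the label on the primary outcome, BACS, from baseline to one named visit. This agrees with the regression, which already uses BACS. State the source of the reliability and SD.
2. Call the classes reliable improvement and no reliable improvement.
3. Report the cross-validated AUC of baseline BACS alone, in the same folds, beside the EEG classifier. Claim EEG prediction only for what it adds to that benchmark.
4. State that the label does not separate therapy benefit from retest gain. Use a practice-adjusted index at most as a sensitivity analysis: it relies on an outside retest estimate and makes the responder class smaller.

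The cost is a few sentences and one extra model, with no new data. The downside is a possibly less favourable EEG claim.

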### Trial design

The design is a single-blind, randomised controlled trial to examine the equivalence of CCT and CIRCuiTS. The trial also aims to examine if MMN at baseline can predict response to the compensation and adaptation therapies and if MMN improves from baseline to post-treatment.

The study will include 100 clinically stable patients with a schizophrenia spectrum disorder. Participants will be randomised in a 1:1 ratio to join either the CCT group or the CIRCuiTS group. Participants will all be active cases in Metro South Addiction and Mental Health Services (community based). Participants in the study will continue to receive standard clinical care (i.e. there are no restrictions on medication or psychosocial interventions, apart from participants receiving therapies addressing neurocognition). These two interventions will be delivered by trained mental health staff once (CCT 2-h session) or twice (CIRCuiTS 1-h sessions) per week for 12 weeks. Groups will be based on a maximum of 6 participants per facilitator. Individual clinical assessments will be at baseline, at post-treatment, and at 3-month follow-up. Randomisation will be carried out using a computer-generated randomisation table.

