### Sample size

In this equivalence study, we will focus on the primary outcome of cognition. We based our power analysis specifically on the BACS. We estimate a dropout rate of 15–20% (from treatment to 3-month follow-up) resulting in a final sample size of approximately 80 participants who will complete the study. This estimate is based on the dropout rates for studies with participants with serious mental illness as well as our experience with group randomised controlled trial research. Due to practicalities of group size and opportunities for running groups over the study timeframe, the maximum number of participants was set at one hundred.

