## Methods: data collection, management, and analysis

### Data collection and statistical methods

The primary efficacy analysis will assess average treatment group differences for the primary outcome measure BACS, over the entire study period (baseline, post-intervention, follow-up), and will use a likelihood based mixed-effects model, repeated measures (MMRM) approach. The MMRM model includes the fixed, categorical effects of treatment (CCT or CIRCuiTS), visit (baseline, 12 and 24 weeks), and treatment-by-visit interaction, as well as the continuous, fixed covariates of baseline score and baseline score-by-visit interaction. The MMRM includes all available data at each time point and is the preferred method of analysing clinical trial data in psychiatry as compared to more traditional repeated measures analysis of variance (ANOVA) and analysis of covariance (ANCOVA) models. Planned comparisons will be done with the MMRM models to determine between-group differences in change of symptoms measures from baseline to weeks 12 and 24. Results from the analysis of dichotomous data will be presented as proportions, with 95% confidence interval, and Fisher’s exact *p* value where appropriate. Non-parametric statistics will be used when assumptions for parametric methods are violated. Effect sizes will be calculated using Cohen’s guidelines. All tests of treatment effects will be conducted using a two-sided alpha level of 0.05 and 95% confidence intervals.

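### The MMN question concerns change by post-treatment, but the ANOVA names no baseline-to-week-12 contrast, and its stated follow-up depends on interactions that do not bear on that question

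*Protocol article*

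**What the plan says.** Under Trial design, the protocol article sets as an aim to examine "if MMN improves from baseline to post-treatment". That is one interval and one direction.

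The section on single-channel and behavioural analyses gives its ANOVA the same purpose: "To investigate if MMN improves after the compensation and adaptation therapy programmes". The model is a repeated measures 2 × 2 × 3 ANOVA on mean ERP values at Fz. Its factors are volatility (stable, volatile), treatment (CCT, CIRCuiTS) and "visit (baseline, 12 and 24 weeks) as factors". A second ANOVA of the same shape is planned for regularity learning, also to examine improvement.

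The paragraph closes with the follow-up rule: "Significant interactions will be further analysed using paired" *t* tests. From its position it appears to cover both ANOVAs. No contrast or follow-up is named for the visit main effect.

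The section Data collection and statistical methods does plan comparisons from baseline to weeks 12 and 24. Those are between-group comparisons within the MMRM models, not within-person change in MMN.

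**The concern.** If MMN improves similarly in both arms and both volatility conditions, the improvement sits in the visit main effect. With three visits this is an omnibus test that the three means are equal. A significant result says that some visit differs from another, without saying which or in which direction. The stated question is about the first interval alone.

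The pairwise comparisons that could answer it are tied to interactions. An interaction with visit means that change differs by arm or by condition, which is a separate question. So the document attaches its pairwise step to terms that do not carry the effect asked about, and attaches none to the term that does.

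At stake is what the MMN result can support. A change appearing only at 3-month follow-up could give a significant visit effect, and the plan names no test that separates it from a change present at the end of therapy. The same holds for regularity learning.

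**Working it through.** **Inputs from the protocol article.** At most 100 randomised, 1:1, with 15–20% dropout (Trial design; Sample size). Three visits and two conditions, so six measurements per person. Two-sided alpha of 0.05; this is stated for tests of treatment effects and is assumed here to apply to each ANOVA F test.

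**The plan's own figure.** 100 × (1 − 0.20) = 80 and 100 × (1 − 0.15) = 85. The stated figure of approximately 80 completers is reproduced at the upper dropout rate; 40 per arm is used below. The article gives no SD, correlation or effect size for MMN, so those are assumptions.

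**Assumptions, set A.** Total SD 1, correlation 0.6 between any two of a person's six measurements, shift of 0.25 SD in both arms and both conditions.

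*Step 1: direct contrast.*
- Error variance per visit, averaged over two conditions: (1 − 0.6)/2 = 0.20.
- Standard error of week 12 minus baseline: √(2 × 0.20/80) = 0.0707.
- Standardised effect: 0.25/0.0707 = 3.54.
- Power of the two-sided paired test: about 94% (simulation, 3,000 replicates: 94.0%).

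*Step 2: visit main effect, gain present at weeks 12 and 24.*
- Visit means (0, 0.25, 0.25); sum of squared deviations 0.0417.
- Noncentrality: 80 × 0.0417/0.20 = 16.7, on 2 and 156 degrees of freedom.
- Power: about 96% (simulated 95.7%).

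*Step 3: visit main effect, shift at week 24 only.*
- Visit means (0, 0, 0.25); sum of squared deviations again 0.0417, so noncentrality is again 16.7.
- Rejection: about 96% (simulated 96.2%).
- Week 12 minus baseline: true difference zero, so it rejects at about its nominal level (simulated 5.4%).

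The omnibus test has the same chance of rejecting in Steps 2 and 3, so significance alone cannot tell the two patterns apart.

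**Second variance structure, set B.** Variance shares: subject 0.50, subject-by-visit 0.15, subject-by-condition 0.10, residual 0.25; 6,000 runs per scenario. With a 0.3 SD shift at week 24 only, the visit test rejects in 97% and the baseline-to-week-12 test is significant in the improving direction in 2.6%. With a sustained 0.2 SD gain, the visit test rejects in 69% and the direct contrast in 66%. The pattern is the same.

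**How often the stated follow-up opens.** Three of the four interactions involve visit. If none is real:
- any of the three significant: 1 − 0.95³ = 14.3% (simulated 13.8% in set A, 14.6% in set B);
- any of all four significant: 1 − 0.95⁴ = 18.5% (simulated 18.6% in set B).

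These figures require equal gains across arms **and** across stable and volatile conditions. With arms equal and an average gain of 0.4 SD, but conditions unequal (set B), at least one visit interaction is significant in:

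| Gain in one condition / the other | Follow-up opens |
|---|---|
| 0.4 / 0.4 SD | 14.6% |
| 0.5 / 0.3 SD | 50% |
| 0.6 / 0.2 SD | 97% |
| 0.8 / 0 SD | about 100% |

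The average improvement is identical in all four rows. Access to the pairwise comparison is governed by how much the conditions differ, not by whether MMN improved.

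**The case against.** The strongest reply is that the visit main effect is itself a planned test of change and loses no sensitivity: 96% against 94% in the common-gain scenario. This stands. A reader might infer from the 14% that the plan rarely tests its hypothesis. The documents do not support that, because it leaves the visit test out of the count. What the visit test lacks is the ability to place the change before post-treatment.

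A reader might also infer that worsening would be taken for improvement. The visit test does reject equally often for either direction (69% each for 0.2 SD in set B). But so would any two-sided test, including the proposed contrast; the sign is read from the means, and nothing in the article suggests it would be ignored.

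A third inference is that the plan bars follow-up of a significant visit effect. It does not: the word only is absent, and a full analysis plan may add such a comparison. The article does, however, fix a follow-up rule and places it on the interactions, so the point goes beyond a detail left unsaid.

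Nor does the article predict equal MMN change in the two arms. Equivalence is set for neurocognitive deficits, with BACS as primary outcome. Equal gains across conditions cannot be presumed either, since volatility is a design factor. The 14% is therefore the low end of a range.

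Finally, the whole-scalp full factorial analysis also includes visit. It names no directional baseline-to-post-treatment contrast, so it does not close the gap.

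**Conclusion.** The point holds as a mismatch between the stated question and the named tests. The planned ANOVA can detect that MMN changed over the three visits, about as well as a direct contrast, but it does not establish that the change occurred by post-treatment. Under the assumptions shown, the visit test rejects in about 96% of trials when the shift comes only at week 24, against about 5% for the contrast that matches the question. The stated pairwise follow-up opens in about 14% of trials (18.5% counting all four interactions) when gains are equal across arms and conditions, rising towards 100% as gains diverge by condition.

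The percentages rest on assumed effect sizes and variance structures, 80 completers and 0.05 per F test. The argument that the omnibus test cannot locate the change does not depend on them. MMN is a secondary outcome, and the BACS analysis is not touched. This is a worthwhile, inexpensive correction and not a threat to the trial's main conclusion.

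**What to change.** In the section on single-channel and behavioural analyses, prespecify week 12 minus baseline, averaged over arms and volatility conditions, as the test of whether MMN improves. Report the signed estimate and 95% CI whatever the interaction tests show, and state which sign counts as improvement. Add week 24 minus baseline as a secondary contrast. Keep the interaction tests to describe differences in change by arm or volatility. Apply the same wording to regularity learning.

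The cost is a sentence or two of analysis text and no new data. The downside is one or two more prespecified contrasts per outcome.
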